### Measurements – links between trauma exposure, PTSD and psychosis

See Table 3, Tertiary outcome measurements. Note that the measurements of psychosis mentioned in Table 2 are necessary, too, for examination of the tertiary objectives.

T.TIP screener*,* including the TSQ*.* The T.TIP screener is designed for the purpose of briefly asking: a) about having experienced overwhelming or life threatening experiences (‘yes’ or ‘no’); and b) If ‘yes’, then participants are asked what kind of PTSD DSM-IV-TR criterion A traumatic events they have experienced: physical abuse, sexual abuse, emotional abuse, extreme neglect and/or accidents/disasters/war. Because patients in this specific patient population may also have experienced traumatic events during psychotic episodes, this category was added. For each category of traumatic events the participant chooses between ‘yes, one traumatic experience’, ‘yes, more than one traumatic experience’ or ‘no traumatic experience’. c) To gain more information about the phenomenological similarities between trauma content and content of the symptoms of their psychosis, participants are asked about similarities (‘no similarity at all’, ‘some similarity’ or ‘strong similarity’). d) Participants then answer questions about PTSD symptoms they may suffer, using the TSQ [36]. The TSQ is a 10-item scale with the five re-experiencing items and five hyperarousal items of the PSS-SR. All items are answered with binary ‘yes' (symptom is present two times a week or more) or 'no’ (symptom is not present or present once a week) responses; the minimum score is zero and the maximum score is ten. The TSQ has a good sensitivity in assessing potential PTSD in crime victims (0.76) and rail crash victims (0.86), as well as a high specificity in both of these groups (0.93 and 0.97, respectively) [36]. The TSQ has also shown to be a good measure to predict future PTSD in assault victims, with a sensitivity of 0.85, a specificity of 0.89, and an efficiency of 0.90 [104]. Both studies mentioned above [36,104] calculated that the optimum cut-off score is 6; any combination of six or more re-experiencing or hyper arousal symptoms predicts PTSD best. The TSQ is not yet calibrated for people with psychotic disorders.

**Table 3 T3:** Measurements tertiary objectives: links between trauma exposure, PTSD and psychosis

**Tertiary outcome**	**MeasurementInterview(i)self-report(s)**	**Screening**	**T0 baseline**
Trauma categories; PTSD risk	T.TIP screener /TSQ (s)	x	
Traumatic events	ITEC (i)		x

*ITEC* Interview for Traumatic Events in Childhood, *T.TIP screening/TSQ* TTIP screening including the Trauma Screening Questionnaire.

The Inventory of Traumatic Events in Childhood (ITEC) [65] is used to interview the participant for traumatic events in his or her life. The ITEC consists of five subcategories: sexual abuse, physical abuse, emotional or psychological abuse, emotional and physical neglect, and ‘other traumas’ that include items such as disaster, war, accidents, illness and death of loved ones. Within each category (for example, physical abuse) a number of specific events are presented (for example,‘You were beaten or got punched’). The participant has to respond to several questions: ‘Did this ever happen to you? ‘, ‘Who did this to you?’, ‘How old were you when this happened?’, ‘Did this occur once, or more?’

For the purpose of the study (a) a category of traumatic events during psychotic episodes was added. This category includes specific events such as ‘A psychosis in which you hurt yourself or tried to kill yourself’; ‘a psychosis in which you were locked up or tied up against your will?’; and b) an assessment was added of both intensity (SUD) and frequency of intrusions for each reported traumatic event. The psychometric properties are good [65]. The scales had good internal consistency (>0.70), except for the physical neglect subscale and an excellent (>0.90) inter-rater reliability. The scales were highly associated with equivalent scales of the Childhood Trauma Questionnaire (CTQ) (that is, good convergent validity) and showed good correspondence with patient file information (that is, good criterion validity). Internal reliability of the ITEC subscales range from .58 to .89 with a mean of .79. The reliability for the physical neglect scale is inadequate, while the other scales display moderate to good reliability. Results showed excellent agreement between the raters for most subscales (intraclass correlation coefficient (ICC) sexual and physical abuse = 1.00; ICC emotional abuse and neglect = .99; ICC witnessing physical abuse = .88; ICC witnessing emotional abuse = .96) and good agreement for the physical neglect scale (ICC = .72). Additionally, high correlations with the corresponding subscales of the CTQ [105-107] were obtained, indicating good convergent validity. Finally, criterion validity was assessed by comparing the presence of maltreatment as mapped by the ITEC with patient file information. Data indicated that the ITEC's sensitivity was excellent, and their scores on their parallel ITEC subscales uniquely predicted sexual and physical abuse and neglect. This was not the case for emotional abuse.

### Measurement – moderators, mediators and predictors of treatment outcome

See Table 4, Quaternary measurements. Note that only measurements on participant variables are included. Look at the therapist ratings section for explanation of measurements of therapist variables.

The Bullying Questionnaire (BQ) [108,109] is used to collect information about being severely bullied in childhood (age <17) as a predictor variable of treatment outcome. The BQ is derived from the original Olweus Bully/Victim list, which has 40 items. The BQ has five items. The BQ questions have been used in the European network of national schizophrenia networks studying Gene-Environment Interactions (EU-GEI). The BQ questions are taken from the Environmental Risk (E-Risk) longitudinal twin study which they adapted from Olweus and have used in several publications, showing good test-retest reliability [108] and reasonable inter-raterreliability [110].

Participants answer if they have been bullied by other children, if they have been physically hurt or injured by other children, if they have been hurt emotionally or psychologically, how severe the bullying was, and if they ever have bullied other children themselves. Scores are on a range from zero (‘never’ or ‘not’) to four (‘often’ or ‘severe’) and total scores of the BQ thus range from 0 to 20.

The Tonic Immobility Scale–Adult Form, Part 1- Short Version(TIS-A-1-SF) [111]) is used to study tonic immobility as a predictor of treatment outcome. TI as a reaction to a traumatic event is originally found mostly in sexually abused women [112] but is also known to occur during other traumatic events. The original TIS-A-Part 1 addresses symptoms of tonic immobility and peritraumatic fear and perceived inescapability [113]. Thus, this TIS-A-Part 1 score represents the individual’s experience of various aspects of the TI response during the traumatic event. The TIS-A-Part 1-Short Form specifically addresses TI. It consists of four items, assessing four possible responses during the traumatic event: (1) freezing, (2) immobility, (3) not being able to shout or scream and (4) possibility of escaping the situation. Answers are on a 7-point Likert-type scale (0 to 6). Psychometric properties of the original TIS-A scale [113] were good, but no data are available with regard to the short version used in the T.TIP study.

**Table 4 T4:** Measurements quaternary objectives: predictors, moderators, mediators (participant variables)

**Quaternary outcome**	**MeasurementInterview(i)self-report(s)**	**T0 baseline**	**T1 midtreatment**	**Within-session (1 to 8)**	**T2 posttreatment**	**T6 FU 6 month**	**T12 FU 12 months**
Bullying	BQ (s)	x					
Tonic immobility	TIS-A-1-SF (s)	x					
Working memory	RIR	x					
Credibility participant	CS-PF (s)			1, 8			
Burden participant	BS-PF (s)			1, 8			
Harm expectancy pre	session rating (s)			2, 3			
Harm experience post	session rating (s)			2, 3			
Demographics	TDQ	x					
Self esteem	SERS-SF (s)	x	x		x		
Illness beliefs	PBIQ (s)	x	x		x		
Post trauma cognitions	PTCI (s)	x	x		x	x	x
Cognitive bias	DACOBS (s)	x	x		x		
Memory	MCQ-RF (s)			2, 3, 8			
Social support	MOS-SSS (s)				x		

*AVH-BAS* Auditory Verbal Hallucinations Basic Assumptions Scale, *BQ* Bullying Questionnaire, *BS-PF* Burden Scale – Participant Form, *DACOBS* Davos Assessment of Cognitive Biases Scale, *FU* follow up, *MCQ-RF* Memory Characteristics Questionnaire – Revised Form (adapted for T.TIP), *MOS-SSS* Medical Outcome Studies - Social Support Survey, *PBIQ* Personal Beliefs about Illness Questionnaire – Revised version, *PTCL* Posttraumatic Cognitions Inventory, *RIR* Random Interval Repetition, *SERS-SF* Self Esteem Rating Scale - Short Form, *TDQ* T.TIP demographic questionnaire, *TIS-A-1-SF* Tonic Immobility Scale- Adult Form-Part 1-Short Form.

The auditory Random Interval Repetition (RIR) task is a computerized reaction time task, that is studied as a possible predictor and moderator of treatment outcome. During this task participants wear headphones that present repetitive beeps of 200 Hz, each lasting for 50 ms. The inter-stimulus-interval (ISI) on this computerized RIR task is either 850 or 1450 ms. Participants are instructed to respond as fast as possible by pressing a bar, every time they hear a beep, and the reaction time (RT) is the dependent variable. The RIR task is carried out under two conditions of three minutes each: 1) while making a distracting task, in this case eye movements, elicited by the index-finger of the research assistant, moving horizontally at 30 cm from the eyes at a pace of two seconds per cycle, and 2) without a distracting task. The order of the conditions is counterbalanced to control for carry over effects. The degree to which eye movements tax the central executive component of the working memory is operationalized as the slowing down of RTs and reduced accuracy (more errors and non-responses) during the distracting task compared with the no-distracting task condition. The task is constructed and performances measured with E-Prime 1.2 software.

To have a RT task carried out while the subject is being distracted simultaneously, is a valid way to assess the presence and severity of cognitive taxing [114]. RTs to auditory cues presented at an RIR task, provide a valid and highly sensitive measure of taxation of the central executive component of the working memory [115]. Laboratory experiments with undergraduates have shown that 1) making eye movements during a stimulus discrimination task slows down RTs and raises the number of errors made [116] and 2) more taxing of the working memory results in higher RTs, more errors and more non-responses [117]. In a pilot study with 12 patients with a psychotic disorder we found the same patterns in the performance on the RIR task with three conditions: no eye movements, eye movements at one second per cycle and eye movements at two seconds per cycle (publication in preparation). In T.TIP two seconds per cycle will be used.

Several measures of treatment credibility, burden, harm expectancy and harm experience are administered to both therapists and participants.

First, the T.TIP Therapist attitude questionnaire (T-TAQ) aims to measure therapist attitude towards the treatments (PE and EMDR). This has two goals: (i) to study therapist treatment attitude as a predictor variable on treatment outcome, and (ii) to study the impact of training and experience on therapist treatment attitude. The T-TAQ is repeatedly administered in the context of training and supervision sessions. The T-TAQ consists of 15 items, divided into three parts a, b (with within session extension) and c (with within session extension). (a) The Impact of Training and Therapeutic Experience Questionnaire – therapist form (ITTEQ-TF) assesses the therapist factor of ‘Training and therapeutic experience’ in PE and EMDR. In this three item therapist self-report list, therapists disclose on a 1 (‘totally disagree’) to 10 (‘totally agree’) VAS their level of (1) training in EMDR/PE, (2) experience in carrying out EMDR/PE and (3) the number of patients treated successfully using EMDR/PE. (b-1)The Credibility Scale- therapist form (CS-TF). Therapists respond to five treatment credibility statements regarding PE and EMDR on a 1 to 10 VAS: (1) This treatment seems logical to me. (2) This treatment seems scientific to me. (3) If I have a PTSD, I would choose this treatment. (4) This treatment would be effective for most people. (5) If a close friend or relative has PTSD, I would recommend this therapy to them. The CS-TF is an adaptation of the original Credibility/Expectancy Questionnaire [118] which demonstrated high internal consistency within each factor (credibility and expectancy) and good test–retest reliability. (b-2) The Credibility Scale- therapist session form (CS-TSF) is an adaptation of the CS-TF. It is an extra 10-item credibility rating that will be applied within actual treatment sessions (1 and 8); the therapist rates not only his or her own opinions on credibility, but in addition makes an estimation of how he or she expects the participant to rate the credibility of the treatment on the same five questions of the CS-TF ('logical' and so on). (c-1)The Burden Scale-therapist form (BS-TF). Seven questions regarding PE and EMDR assess ‘Perceived barriers’ on a 1 to 10 VAS: (1) PTSD will get worse, (2) psychosis will get worse, (3) other comorbid symptoms will get worse, (4) the treatment is a burden to the patient, (5) the treatment is a burden to the therapist, (6) the treatment will facilitate drop out, (7) the treatment will facilitate crisis or admissions to hospital. The BS-TF is inspired by studies that compare the burden and endorsement of CBT and EMDR (for example, studies using the Distress/Endorsement Validation Scale (DEVS)) [119,120]. The BS-TF is not an adaptation of the DEVS, however. It is adapted to suit the research questions of the study regarding (perceived) barriers for treatment in the population of patients with psychosis. There are no psychometric evaluations available. (c-2) The Burden Scale- therapist session form (BS-TSF) is an adaptation of the BS-TF. It is an extra three-item burden rating that will be applied within actual treatment sessions (1 and 8); the content is limited to estimations by the therapist of how he or she expects the participant to rate the burden of the treatment on a 1 to 10 VAS (‘no, not at all’ to ‘yes, very much’): (1) Does the participant fear treatment?, (2) Is he or she hesitant to have this treatment?, and (3; only for PE) Does the participant expect that listening to the recordings at home will be a burden?

The Treatment Preference and Experience-Therapist Scale (TPE-TS) allows therapists, before treatment starts, to score their treatment experience with both PE and EMDR and their personal preference to start with PE and EMDR with this particular patient, on a VAS-scale from 0 to 100. Post treatment the therapist again scores his/her personal preference to use PE and EMDR with this particular patient using the same scale. Psychometric evaluations are not available.

The Burden Scale – Participant Form (BS-PF) assesses burden in participants before (expected) and after (experienced) treatment in both conditions, PE and EMDR. Before treatment the participants responds on a 10-point Likert-type Scale (‘no, not at all’ to ‘yes, very much’) to the following questions: (1) Do you fear treatment?, (2) Are you hesitant to have this treatment?, and (3, only for PE) Do you expect that listening to the recordings at home will be a burden? After treatment the participant responds on a 10-point VAS (‘no, not at all’ to ‘yes, very much’) to the questions: (1) Do you feel that afterwards the treatment was less burdensome than you had expected?, (2) Was the treatment much of a burden to you?, (3) How much of a burden was it to listen to recordings at home? No psychometric evaluations are available.

The Credibility Scale - Participant Form (CS–PF) assesses credibility before and after treatment in both conditions PE and EMDR. Participants respond on a 10-point VAS (‘no, not at all’ to ‘yes, very much’) to the statements: (1) This treatment seems logical to me, (2) This treatment seems scientific to me, (3) If I have a PTSD, I think this treatment will help me, and (4) If a close friend or relative has PTSD, I would recommend this therapy to them. There are no psychometric evaluations available.

The Harm Expectancy session ratings assess the treatment harm expectancies (before the session) and experienced harm (after the session) in two sessions (sessions 2 and 3). Participants respond on a 10-point VAS (‘no, not at all’ to ‘yes, very much’) to the questions, describing expected or actually experienced fear of going crazy, panicking and losing control, panicking and drop out of the session, or yet another harm expectancy or harm experience.

The T.TIP Demographic questionnaire (TDQ) assesses basic personal, social and medical data as predictors of treatment outcome variables: 1) age; 2) date of birth; 3) country of birth (participant, father, mother); 4) highest level of achievement in education; 5) daily housing/living situation; 6) DSM-IV-TR diagnoses; 7) substance abuse or dependence; 8) current medication; 9) years of illness of psychosis and PTSD.

The Self-Esteem Rating Scale - Short form(SERS-SF) [121] assesses the mediator/moderator variable of self esteem on treatment outcome. The 20-item SERS-SF, with its positive and negative self-esteem subscales, appears to be a valid and reliable self-esteem measure for individuals with severe mental health problems. The original 40-item SERS was reduced to a psychometrically good 20 item version of the SERS, the SERS-SF. The SERS-SF [121] has 10 positive and 10 negative items on self-esteem. The two scales have excellent internal consistency (*α* = .91 positive scale; *α* = .87 negative scale). The test–retest reliability of both scales is high (r =0.90; r =0.91). The SERS total score correlated highly with both scales (r = 0.72 and r = 0.79), indicating good convergent validity.

The Personal Beliefs about Illness Questionnaire – Revised version (PBIQ-R*)*[51] assesses the mediator/moderator variable of cognitions about, and coping with, being ill on treatment outcome. The original PBIQ was a 16-item scale developed to assess people’s appraisals of a psychotic illness in five domains, namely (1) control over illness; (2) self as illness; (3) illness as an impediment to the attainment of goals; (4) humiliation and guilt, and (5) need for social containment. A revised 29-item scale (PBIQ-R) measures five different modes of experience following a psychotic illness: shame (six items); loss (seven items); entrapment in psychosis (six items); control over illness (five items); and social marginalization/group fit (five items). Participants respond to statements (for example, ‘I will always need medical care’) by choosing between: ‘strongly disagree’, ‘diagree’, ‘agree’ or ‘strongly agree’. The PBIQ has no total score. The PBIQ-R has good predictive validity for relapse as a result of negative appraisals of illness and coping skills [122].

The Posttraumatic Cognitions Inventory (PTCI) [93] is assessed as a mediator/moderator variable on treatment outcome. For a description, see the section on Measurements – effects of treatment on psychopathology and cost effectiveness.

The Davos Assessment of Cognitive Biases Scales (DACOBS) [123] assesses the mediator/moderator variable of cognitive biases in psychoses on treatment outcome. Cognitive problems and biases play an important role in the development and continuation of psychosis. The DACOBS has been developed as a self-report measure of these deficits and processes. It assesses seven statistically independent deficient thought processes. Each factor is represented with six items: jumping to conclusions, confirmation bias/dogmatism, selective attention for threat, self as target, theory of mind problems, subjective cognitive failure and avoidance behavior. Each item is a statement that is scored on a 7-point Likert scale within a two-week time frame. Reliability was good (*α* = 0.90; split-half reliability = 0.92; test-retest reliability = 0.86). The DACOBS distinguishes between schizophrenia spectrum patients and normal control subjects. It is reliable and valid and may be used in research.

The Auditory Verbal Hallucinations – Basic Assumptions Scale *(*AVH-BAS*;* [name] *etal*., publication in preparation) assesses the mediator/moderator variable of participants' basic assumptions about voice hearing on treatment outcome. The AVH-BAS is especially developed for this RCT. In another study outside of T.TIP responses of 176 voice-hearing patients were assessed on several items that reflect cognitive and emotional appraisal of voices. After item- and factor-analysis, 14 AVH-BAS-items remained that assess cognitive assumptions about voices. Four factors have shown to be relevant: (1) negative self-esteem, (2) guilt, (3) powerlessness and (4) danger/threat. Initial analyses suggest that the AVH-BAS may be a reliable and valid instrument.

The Memory Characteristics Questionnaire – Revised Form (MCQ-RF) [119], which was adapted for the present study, assesses aspects of the traumatic memory as a mediator/moderator variable and its influence on treatment outcome. The MCQ-RF is administered within treatment sessions. The MCQ-RF assesses self-reported characteristics of trauma memories. The original MCQ has a test-retest reliability total scale of r =. 86. In T.TIP we used a shortened version (three items) of the re-experiencing subscale (test-retest reliability r = .86): sense of reliving, sense of here and now, and perceptual elements. We added one item about memory-related emotions (for example, dissociation, anxiety, anger, guilt and depression) and one item about memory-related image characteristics (for example, color, light and movement). Participants were asked to rate their trauma memories for each of the items on a 0 to 100 scale.

The Medical Outcome Studies - Social Support Survey (MOS-SSS) [120] assesses experienced social support as a possible predictor variable of treatment outcome. The survey consists of four separate social support subscales and an overall functional social support index. A higher score for an individual scale or for the overall support index indicates more support. Overall index internal-consistency reliability: α=0.97, one-year test-retest stability= 0.78. For our purposes only the subscales ‘emotional support’ (ES) and ‘instrumental support’ (IS) are administered to the participants. On a Likert type scale from 1 (‘none of the time’) to 5 (‘All of the time’) participants respond to four ES-items: (1) Someone you can count on to listen to you when you need to talk, (2) Someone to give you information to help you understand a situation, (3) Someone to give you good advice about a crisis, (4) Someone to confide in or talk to about yourself or your problems, and to four IS-items (5) Someone whose advice you really want, (6) Someone to share your most private worries and fears with, (7) Someone to turn to for suggestions about how to deal with a personal problem and (8) Someone who understands your problems.

The internal-consistency reliability and one-year stability for subscales ES and IS: α=0.96, stability =0.72 [120].

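### The only described score for being bullied (BQ, 0 to 20) includes an item on having bullied others; separately, the four social-support items labelled instrumental do not describe practical help

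*Protocol article*

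**What the plan says.** Both instruments are described in the protocol article under Measurement – moderators, mediators and predictors of treatment outcome.

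**BQ.** The purpose sentence says the questionnaire "is used to collect information about being severely bullied in childhood (age <17) as a predictor variable of treatment outcome". On length: "The BQ has five items". The items cover being bullied by other children, physical injury from it, emotional or psychological hurt, severity, and, last, "if they ever have bullied other children themselves". Items run from zero to four, and "total scores of the BQ thus range from 0 to 20". No victim subscore or other scoring is described.

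**MOS-SSS.** The survey "assesses experienced social support as a possible predictor variable of treatment outcome". Only two subscales are given to participants, emotional support (ES, items 1 to 4) and instrumental support (IS, items 5 to 8). After the ES items the text continues "and to four IS-items (5) Someone whose advice you really want, (6) Someone to share your most private worries and fears with". Items 7 and 8 concern suggestions for handling a personal problem and being understood.

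Under Analyses, the article says only that predictors will be assessed with (logistic) regression.

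**The concern.** A predictor score should contain what its stated purpose says it contains. The BQ purpose sentence is about victimization, yet the one score described also rises when the participant reports having bullied others. If that total goes into the regression, an association with outcome mixes the two experiences, and two participants with the same history as victims can receive different scores.

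The MOS-SSS issue is one of labelling. A result published under the name instrumental support would be read as being about practical help, and the listed items do not ask about that.

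Both variables belong to the quaternary objectives. At stake is how an exploratory predictor result is interpreted. The CAPS analysis, the sample size and the error rates are not affected.

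**Working it through.** **1. Reproducing the stated BQ range.** Inputs from the BQ description: 5 items, each scored 0 to 4. The range of a sum is the number of items times the item range.

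- All five items: 5 × 0 = 0 to 5 × 4 = 20, which is the stated range.
- Four victim items only: 4 × 0 = 0 to 4 × 4 = 16.

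The stated maximum of 20 is reached only if the perpetration item is added in the same direction as the victim items. It accounts for 4 of the 20 points.

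**2. What a given total can mean.** Let V be the victim score (0 to 16) and P the perpetration item (0 to 4), so that total = V + P.

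- Never bullied, bullied others at the top category: V = 0, P = 4, total 4.
- One point on each of four victim items, never bullied others: V = 4, P = 0, total 4.
- Total of 10: V lies between 10 − 4 = 6 and 10 − 0 = 10.

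**3. Likely size of the distortion.** The article gives no item variances or correlations, so these are assumptions: unit variance for every item, correlation r between victim items of 0.3 to 0.7, and correlation c of the perpetration item with each victim item of 0 to 0.4.

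- Var(V) = 4 + 12r
- Cov(V, P) = 4c
- Var(V + P) = Var(V) + 1 + 8c
- Corr(V, V + P) = (Var(V) + 4c) / √(Var(V) × Var(V + P))

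| r | c = 0 | c = 0.2 | c = 0.4 |
|---|---|---|---|
| 0.3 | 0.940 | 0.954 | 0.971 |
| 0.5 | 0.953 | 0.962 | 0.973 |
| 0.7 | 0.962 | 0.968 | 0.976 |

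Example, r = 0.3 and c = 0: Var(V) = 7.6, Var(V + P) = 8.6, correlation = 7.6 / √(7.6 × 8.6) = 0.940.

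Over this range the two scores order participants similarly, though not identically.

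**4. MOS-SSS item content.** No arithmetic applies; the items are compared on their wording.

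| Item labelled IS | Content | Nearest item labelled ES |
|---|---|---|
| 5 | advice the participant wants | 3, advice in a crisis |
| 6 | sharing private worries and fears | 4, confiding |
| 7 | suggestions on a personal problem | 2, information to understand a situation |
| 8 | being understood | 1, being listened to |

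Items 5 and 7 read as informational support, and items 6 and 8 as emotional support. None of the four mentions practical or material help. The pairing in the last column is a judgement; the absence of practical help is plain from the wording.

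**The case against.** **BQ.** The instrument is called the Bullying Questionnaire and is derived from a longer bully/victim list. The quaternary objectives and Table 4 name the variable simply as bullying. One item on bullying others fits that name. This stands: the conflict is with the purpose sentence, not with the instrument's name, and four of the five items are on target. The score is contaminated; it would be wrong to say that it does not measure being bullied.

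The article also never says that the 0 to 20 total is the regressor, and the scoring of an exploratory predictor may be settled in an analysis plan that is not shown. That stands too. Even so, the total is the only score described, and it does not match the stated purpose. A reader might infer that any BQ association would be uninterpretable. The correlations above do not support that, and nothing in the article shows how common perpetrators without victimization are.

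**MOS-SSS.** The article does not define instrumental support, and the mismatch may be a naming or translation slip. The declared predictor is social support as a whole; no objective concerns instrumental support by itself. Both points stand and limit this to a check of the label.

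Two stronger readings are tempting. One is that ES and IS would be highly collinear; overlapping wording suggests related scores, but the article gives no correlation between them. The other is that quoting one alpha (0.96) and one stability value (0.72) for both subscales is itself an error; it may be an abbreviated or pooled citation and shows nothing either way.

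**Conclusion.** The point holds in limited form. The BQ total, as described, adds perpetration to a score meant to capture being bullied. This follows from the article's own item list and range and needs no outside source. The distortion is probably modest (correlation with the victim-only score about 0.94 to 0.98), but that figure rests on assumed item variances and correlations.

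The MOS-SSS label does not fit the four items printed under it. This rests on the ordinary meaning of instrumental as practical help and on the items having been administered as printed.

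Both are minor matters confined to exploratory predictors. They are worth correcting because correction is cheap and prevents mislabelled results.

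**What to change.** **BQ.** Define the being-bullied predictor as the sum of the four victim items (0 to 16) and enter the item on bullying others as a separate variable. The items are already collected, so the cost is rescoring plus one more term in the regression.

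**MOS-SSS.** Check the instrumental label against the form actually administered. If the items are as printed, report the eight items as emotional/informational support and draw no conclusion about instrumental support. The cost is that no separate instrumental-support result can be reported. Replacing the questions is not warranted: the Trial status section says recruitment is under way, participants already assessed would lack the new items, and no stated objective needs them.
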